### Study design

2.4

This study is a randomized controlled trial with a stepped-wedge design, where all clusters and participants in clusters receive intervention eventually in random order [43] (Fig. 1). Participants are randomized to either a group starting intervention within 1–3 weeks after the recruitment, or to a waiting-list group. The waiting-list group starts the intervention after the first group has completed the intervention, i.e., after approximately 4 months. Three groups (A, B, C) with 10 subjects each start the intervention immediately, and three groups (D, E, F) with 10 subjects each are on the waiting list.

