**Methods:**

Our purpose here is to provide useful scientific information on the effect of pain-management group participation on chronic pain and pain-related co-morbidities and symptoms, as well as practical information for primary and occupational health services to initiate pain-management group activity.

This study will be carried out at primary care Occupational Health Helsinki (Helsinki city employees' occupational health services), with the Finnish Institute of Occupational Health as the research partner.

This is a stepped-wedge cluster randomized controlled trial among both male and female municipal employees aged 18 to 65, all of whom had visited an occupational doctor, nurse, psychologist, or physiotherapist because of any chronic pain unrelated to malignant disease. An additional inclusion criterion is work disability risk being elevated, based on a short screening questionnaire (modified Örebro questionnaire). Each participant and each interviewer will be blinded at randomization.

Three groups, 10 subjects in each, begin directly after recruitment with 6 weekly 2-h meetings and a follow-up meeting 6 months later. Three waiting-list groups begin 4 months later. Subjects complete self-administered questionnaires before and after the sixth meetings, also 6 months later. Primary outcomes are pain intensity, current work ability, pain self-efficacy, fear-avoidance beliefs, chronic pain acceptance, depressive symptoms, sleep problems, sickness absence days, and number of occupational health care contacts from OH's medical records.

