### Timetable

2.5

Recruitment lasts for 1 month, with the Screening (Scr) Questionnaire (modified Örebro questionnaire), filled out before the interview and during the interview. ABC groups start their six meetings one month after recruitment ends. The before (Bef)1 questionnaire is completed during the interview and returned at the first meeting. The After (Aft) questionnaire is filled out during the sixth meeting. DEF groups are on the waiting list and get their Bef1 questionnaire by mail, while the first three groups (ABC) are in the intervention. Bef1 is returned in one week. DEF start the intervention, six meetings 4 months after the first intervention. The Bef2 questionnaire is sent by mail to the DEF groups before intervention and collected on the first meeting day. The Aft questionnaire is completed at the end of the sixth meeting, and participants are advised to book time for their own occupational health nurse if a group member wishes support in completing the pain management plan. Aft6m is filled out at the 6-month meeting. The Aft12 m is completed in the meeting 12 months after intervention; the Aft12 m meeting is arranged only for the ABC groups (Fig. 2).

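### The start of groups A, B and C is dated inconsistently, and no waiting-list measurement is tied to their post-course questionnaire

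*Protocol article*

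**What the plan says.** **ABC start.**
- Abstract, Methods: the first three groups "begin directly after recruitment with 6 weekly 2-h meetings".
- Section 2.4, Study design: participants go either to a waiting list or to a group "starting intervention within 1–3 weeks after the recruitment". The same paragraph adds: "Three groups (A, B, C) with 10 subjects each start the intervention immediately".
- Section 2.5, Timetable: "ABC groups start their six meetings one month after recruitment ends". The same section states "Recruitment lasts for 1 month".

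**DEF start.**
- Abstract, Methods: "Three waiting-list groups begin 4 months later".
- Section 2.4: the waiting list follows once the first groups have finished their course, "i.e., after approximately 4 months". No origin is given for the 4 months.
- Section 2.5: "DEF start the intervention, six meetings 4 months after the first intervention". It does not say whether this counts from the start or the end of the first course.

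**Questionnaires.** Section 2.5 has ABC fill in Bef1 at the recruitment interview and Aft at the sixth meeting. DEF receive Bef1 by post at some point during ABC's course, with a week to return it, and hand in Bef2 at their own first meeting. Section 2.7 describes Bef1 differently: it follows the interview, with up to a week to respond, and no distinction is made between the arms.

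**Analysis.** Section 2.11 compares post-intervention with pre-intervention (control) periods in linear mixed models and reports a time effect.

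**The concern.** These dates decide when each pre- and post-measure is taken. There are only two start times, and once DEF begin their course nobody is untreated. For the questionnaire outcomes, the randomised between-arm evidence is therefore ABC's Aft against a DEF measure taken while DEF are still waiting. That contrast is clean only if the two measures are taken at about the same time.

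Timing matters more than usual because section 2.1 admits only people scoring 50 or more out of 100 on the modified Örebro questionnaire. Section 2.7 shows that this score contains pain intensity, depressive symptoms and sleep, all of which are also outcomes. Some improvement after screening is expected without any treatment. On the section 2.5 text, ABC's Bef1 sits at the interview, close to that screening score, while DEF's Bef1 comes later. The two arms' baselines would then stand at different points of any such decline.

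**Working it through.** **Inputs**
- 1 month = 365.25 / 12 / 7 = 4.35 weeks, so 4 months = 17.4 weeks.
- Recruitment: 1 month (section 2.5).
- Course: six weekly meetings (section 2.6), which is 5 weeks from first to sixth meeting, or 6 weeks nominally.

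**Step 1. The plan's own figure: course completion at about 4 months (section 2.4).**
- Course alone: 5 / 4.35 = 1.15 months, or 6 / 4.35 = 1.38 months.
- Adding the one-month wait of section 2.5: 2.15–2.38 months after recruitment ends.
- Adding the recruitment month: 3.15–3.38 months after recruitment opens.

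None of these origins gives 4 months, so completion and 4 months are not the same date.

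**Step 2. Age of ABC's Bef1 at the first meeting.** If Bef1 is filled in at the interview, the last person interviewed waits only the stated delay and the first waits the delay plus 4.35 weeks. Adding 5 weeks gives the interval from Bef1 to Aft.

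| ABC start after recruitment ends | Bef1 age at first meeting (weeks) | Bef1 to Aft (weeks) |
|---|---|---|
| 0 weeks (abstract) | 0–4.3 | 5–9.3 |
| 1–3 weeks (2.4) | 1–7.3 | 6–12.3 |
| 4.35 weeks (2.5) | 4.3–8.7 | 9.3–13.7 |

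The section 2.5 delay exceeds the upper limit in section 2.4 by 4.35 − 3 = 1.35 weeks. Counting from each person's own recruitment does not help: section 2.5 then implies a wait of 4.3–8.7 weeks against 1–3 weeks. Using the one-week response time of section 2.7 lowers the ages by at most a week.

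**Step 3. Gap from ABC's Aft to DEF's Bef2** (taken at DEF's first meeting).
- 4 months from ABC's start: 17.4 − 5 = 12.4 weeks.
- 4 months from ABC's sixth meeting: 17.4 weeks.

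**Step 4. Gap from DEF's Bef1 to ABC's Aft.**
- Section 2.5: posted anywhere within a 5-week course, so 0–5 weeks before Aft at posting, with a further week to return it.
- Section 2.7: soon after the interview, so 5–13.7 weeks before Aft across the rows above, less up to one week of response time.

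DEF's two untreated measures therefore lie on either side of ABC's Aft. One has no fixed date, and the other comes about 12 or 17 weeks later.

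**The case against.** **The DEF dates.** A reader might infer that the DEF statements contradict each other as plainly as the ABC ones, with DEF perhaps starting the moment ABC finish and Bef2 coinciding with Aft. The documents do not support that. Section 2.4 puts DEF's start after ABC's completion, which sets an order, and then dates it at about 4 months. No section has DEF starting on completion. The abstract counts start to start, and section 2.5 can be read the same way. All three then fit ABC start plus 4 months, provided one passes over the equation of completion with 4 months in section 2.4. This objection stands, and it limits the DEF part to loose wording.

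**Existing control measures.** DEF's Bef1 is an untreated measure that, under section 2.5, falls inside ABC's course whichever start date applies. So it would be wrong to say that DEF have no control measure near ABC's Aft. What remains is that Bef1 is not fixed to Aft, and that section 2.7 can place it weeks earlier.

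**Size of the conflict.** The wording in the abstract, and the word for ABC's start in the last sentence of section 2.4, may only contrast ABC with the waiting list. The nearest numerical statements differ by about 1.4 weeks, and the baseline-age ranges overlap. It is therefore too strong to call the intervals undefined: they are not fixed, within the ranges shown. Figures 1 and 2 are not reproduced in the text at hand, and Figure 2 may give a single timeline. That would not remove the disagreement between the sections.

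**Bias.** Both arms pass the same screen, the model includes time, and section 2.2 remarks that pain often does not change in treatment studies. These points temper the concern. They do not supply a simultaneous control observation.

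**Conclusion.** The ABC start is stated in ways that cannot all hold, and the age of ABC's baseline at the first meeting moves from about 0–4 weeks to 4–9 weeks with the statement chosen. For DEF, section 2.4 equates a course of about 1.2–1.4 months with 4 months, and section 2.5 leaves its origin open. The statements can still be reconciled as ABC start plus 4 months, which puts Bef2 about 12 weeks after ABC's Aft (about 17 weeks on the other count).

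On that favourable reading too, no untreated DEF measure is tied to ABC's Aft. The time effect at Aft must then be interpolated between DEF measures at other dates, or assumed constant over several weeks. The treatment estimate depends on that assumption in people selected on scores that overlap the outcomes.

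These are calendar gaps only. The documents give no standard deviation or test–retest correlation from which to size a bias, so none is claimed. The figures assume that Bef1 is filled in at the interview and that weekly meetings run without a break.

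**What to change.** 1. Reconcile the abstract and sections 2.4, 2.5 and 2.7 to one start date per arm, each with a stated origin, and to one rule for when Bef1 is completed in each arm. Which dates apply is for the investigators to decide.
2. Whatever schedule is kept, tie one DEF waiting-list questionnaire to the week of ABC's sixth meeting and name it as the concurrent control for ABC's Aft.
3. Keep a DEF baseline at the interview, so that both arms start from a measure taken at the same stage.

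The cost is wording in four places and at most one extra mailing to the 30 DEF participants. The number of participants and the course itself do not change.

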**Fig. 1 fig1:**
[figure not shown]
Study design of a stepped-wedge cluster randomized controlled trial. Shaded cells are intervention periods, and blank cells are control periods. This trial has six data-collection points. Surveys: Scr = screening, Bef1 = before intervention (1st time), Bef2 = before intervention (2nd time), Aft = immediately after intervention, Aft6m = 6 months after intervention, Aft12 m = 12 months after intervention, for only half of the clusters.

The participants’ own OH nurses and doctors are informed about the study and are responsible for the participants' medical care as usual, if needed. The researchers ([name], [name]) are not involved in treating the study participants during the study, to prevent any influence on the results. No restrictions exist in initiating or changing the pain medication or other treatment modalities or examinations during the study.

### Timetable

2.5

Recruitment lasts for 1 month, with the Screening (Scr) Questionnaire (modified Örebro questionnaire), filled out before the interview and during the interview. ABC groups start their six meetings one month after recruitment ends. The before (Bef)1 questionnaire is completed during the interview and returned at the first meeting. The After (Aft) questionnaire is filled out during the sixth meeting. DEF groups are on the waiting list and get their Bef1 questionnaire by mail, while the first three groups (ABC) are in the intervention. Bef1 is returned in one week. DEF start the intervention, six meetings 4 months after the first intervention. The Bef2 questionnaire is sent by mail to the DEF groups before intervention and collected on the first meeting day. The Aft questionnaire is completed at the end of the sixth meeting, and participants are advised to book time for their own occupational health nurse if a group member wishes support in completing the pain management plan. Aft6m is filled out at the 6-month meeting. The Aft12 m is completed in the meeting 12 months after intervention; the Aft12 m meeting is arranged only for the ABC groups (Fig. 2).

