### Randomization

2.3

Occupational health nurses, doctors, and psychologists and physiotherapists are responsible for recruiting 60 mainly Finnish study participants and know well the participants’ medical history and with the participants go through all inclusion and exclusion criteria. Meta-analysis by Bernardy et al., in 2010 involved whether CBT has any effect on fibromyalgia symptoms. The median number of patients with CBT was 40, with group size ranging from 7 to 64. Of the 527 patients in the CBT groups, 81% and in the control groups 75% completed therapy [20]. Consistently, we estimate those, who will take part in our study as ranging from 75% to 81%. Choice of the final sample size is influenced also by its being unethical to have a large sample if the benefit of treatment is unknown. Final sample size is also influenced by the adequacy of financial resources. We will ask for voluntary group leaders among its personnel: psychologists, nurses, and physicians. Moreover, we will recruit one pain nurse from the hospital pain clinic. Three tutor pairs comprise group leaders. In each patient group will be 10 participants, the recommended group size (8–10 participants) for the tutor to be able to work with every participant during the 2-h meeting. Six groups with 10 participants each is estimated to provide sufficient data for the statistical analyses, with no pilot study data.

Since this intervention includes pain psychotherapy (CBT, mindfulness, attendance, and commitment therapy ACT) with topics about chronic pain differing in every meeting, including homework, increasing the sample size to account for dropout is not recommendable. With increasing sample size, new participants would not take part in all group meetings, which could weaken peer support and reliability and the validity of research results. Subjects who fulfill the inclusion criteria (Table 1) and express an interest in participating in the study will be individually interviewed ([name], [name]). In this interview, inclusion and exclusion criteria will be topics asked about, in person. All will be informed about the study, and provide their written informed consent including their participation as being voluntary. They will receive information stating that during the study, each subject is able to use occupational health services as before. During the recruitment phase, the subjects fill out the short screening questionnaire (Scr), the modified Örebro questionnaire.

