Sixth meeting:	• Themes of the meeting: new tools to improve pain management, making one's pain management plan • Filling out the follow-up inquiry • Discussion of homework and pain management tools. • Homework: The pain management plan will be given for writing at home
Seventh meeting, 6-month follow-up, Eighth meeting 12-month follow-up for ABC groups	• Themes of the meeting: psychological flexibility, importance of training and awareness skills, work as rehabilitation • Updating the pain management plan

Both participants and interviewers are blinded for the randomization, and at the end of the interview participants are randomized to one of the six groups (A, B, C, D, E, F). In this stepped-wedge design, every participant knows that he or she will receive an intervention, and the researchers know that no one will be left without treatment, which is not the case in conventional RCT [43].

The request for pain-management group activity originates with the patients themselves. Occupational Health Helsinki has provided three other kinds of groups during the previous 5 years (groups for sleep problems, depression, and burnout). The practical framework for our pain-management group is based on the feedback from those groups (size, facilities, timing, length, language, visual tools). After discussion between the leadership of the city of Helsinki and Occupational Health Helsinki, the results of this study will be provided to the participants in the form of the result report (via e-mail) as well as articles in the media (OHC website, Twitter and such).

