*Work ability variables*	Current ability to do light work for an hour (0 = can do despite pain, 10 = can't do at all because of pain)	x	x	x	x
	Self-estimated work ability in 3 months, 2 items (0 = very large chance, 10 = no chance)	x	x	x	x
	Sickness-absence days during the past 30 days (0–30)		x	x	x
	Sickness-absence days for pain during the past 30 days (0–30)		x	x	x
*Other*	Days enjoying life during the past week (0–7)		x	x	x
	Days feeling active and energetic during the past week (0–7)		x	x	x
	Days feeling tense or restless during the past week (0–7)		x	x	x
*Covariates*	Age	x			
	Gender	x			
	Occupational title		x		
	Height		x	x	x
	Weight		x	x	x
	Physical exercise, number of times per week		x	x	x
	Kind of sport/sports, open question		x	x	x
	Chronic disease, (0 = no, 1 = yes)		x	x	x
	Chronic disease, if yes, which, open question		x	x	x
	Smoking, (0 = no, 1 = no, quit, 2 = yes)		x	x	x
	Quit smoking, years smoked		x	x	x
*Benefits of*	Usefulness of mindfulness practice (0 = not at all useful, 10 = very useful)			x	
	Usefulness of peer group for different issues, 17 items (0 = not at all helpful, 6 = very helpful)			x	
	Ranking importance of features of peer group (1 = most helpful, 2 = next most helpful, etc.) 5 items			x	
	Benefit from participating in pain- management group (0 = not at all useful, 10 = very useful)				x

After the recruitment and interview, the baseline questionnaire (Bef1) is completed or subjects are given a 1-week response time. The waiting-list group fill out an additional questionnaire during the waiting-list period (Bef2). After intervention, the first follow-up questionnaire (Aft) is filled out, and the second follow-up questionnaire (Aft6m) at the 6-month follow-up group meeting (seventh meeting). The third follow-up questionnaire (Aft12 m) is sent via mail only for the first intervention group.

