### Statistical analysis

2.11

The post-intervention period is compared with the pre-intervention (control) period. Linear mixed-effect models allow analysis of repeated measures data and the differences in the outcomes of interest between intervention and control periods. Intention-to-treat analyses are conducted, and time-effect and intra-cluster correlation coefficients reported. When the null hypothesis (i.e., no difference) is rejected, it is always possible to conclude, whatever the results of the study are, that there exists a difference but actually there is not (type-I error or false positive) [51]. Since the sample size is rather small, exact confidence interval for outcomes will be the choice to avoid statistical bias and false-positive or false-negative errors [51].

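### Aft and Aft6m are collected at group meetings with no stated route for those absent, so intention-to-treat for the seven questionnaire outcomes is exposed to attendance-related selection

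*Protocol article*

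**What the plan says.** The protocol article fixes how each questionnaire is collected.

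- **Aft.** Section 2.5 states for groups A, B and C: "The After (Aft) questionnaire is filled out during the sixth meeting". For D, E and F it states: "The Aft questionnaire is completed at the end of the sixth meeting". Table 1 lists "Filling out the follow-up inquiry" among the activities of meeting six.
- **Aft6m.** Section 2.5: "Aft6m is filled out at the 6-month meeting". Section 2.7 agrees, placing "the second follow-up questionnaire (Aft6m) at the 6-month follow-up group meeting (seventh meeting").
- **Aft12m (A, B and C only).** Section 2.5 has it completed in the 12-month meeting. Section 2.7 says: "The third follow-up questionnaire (Aft12 m) is sent via mail only for the first intervention group".
- **Pre-intervention forms.** Under Section 2.5, A, B and C complete Bef1 at the interview and return it at the first meeting. D, E and F get Bef1 by mail and return it within a week. Their Bef2 is mailed and collected on the first meeting day.
- **Register data.** Under Section 2.7, sickness absence and use of occupational health services come from the patient register.

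On participation, Section 2.3 says "we estimate those, who will take part in our study as ranging from 75% to 81" per cent and argues against enlarging the sample for dropout. On analysis, Section 2.11 says "Intention-to-treat analyses are conducted", using linear mixed-effects models for repeated measures.

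**The concern.** Intention-to-treat needs outcome data on everyone allocated, including those who stop attending. Here the two main post-intervention forms are filled in at a treatment session, so a person who misses that session supplies no value unless someone acts outside the written schedule. The plan itself expects a sizeable minority not to take part. Section 2.1 also recognises the link, because it excludes severe disease partly on the ground that meetings could be missed and follow-up lost.

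The randomised comparison is touched directly. While A, B and C are in the intervention, D, E and F return Bef1 by post with no attendance condition. The treated values set against it come from those who were in the room. If people who gain little are more likely to stay away, the remaining treated values look too good. Seven of the nine outcomes in Section 2.8 are affected, including pain intensity, on which the sample size rests. Outcome data that are never collected cannot be recovered at the analysis stage.

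**Working it through.** **Inputs**

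- Detectable difference (Section 2.2): 15% of a mean of 7.14, so 0.15 × 7.14 = 1.071 points. It serves here only as a scale. The sample size of 60 cannot be checked uniquely, because the article gives no SD or intra-cluster correlation, but this point does not depend on it.
- Participation (Section 2.3): a = 0.81 or 0.75. These are the therapy-completion figures of the CBT and control groups in the cited fibromyalgia meta-analysis. Applying them to presence at meeting six is an assumption.
- Share of the attenders' gain that absentees obtain: f. The article does not give it, so a range is shown.

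**Step 1: who lacks a form.** 60 × 0.19 = 11.4 and 60 × 0.25 = 15. About 11 to 15 of 60 would have no Aft value.

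**Step 2: size of the distortion when absence is tied to benefit.** With attenders gaining Δ = 1.071:

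- effect in all allocated = Δ × [a + f(1 − a)]
- attenders' estimate = Δ
- overstatement = 1 / [a + f(1 − a)] − 1

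| f | a | a + f(1 − a) | Effect in all allocated | Overstatement |
|---|---|---|---|---|
| 0 | 0.81 | 0.810 | 0.87 | 23% |
| 0 | 0.75 | 0.750 | 0.80 | 33% |
| 0.5 | 0.81 | 0.905 | 0.97 | 10% |
| 0.5 | 0.75 | 0.875 | 0.94 | 14% |
| 1 | either | 1 | 1.07 | 0% |

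**Step 3: does the planned mixed model repair this?** A small simulation used 60 people, period effects, a random intercept per person, treatment patterns 0-1-1-1 for A, B, C and 0-0-1-1 for D, E, F, between-person SD 1.4, within-person SD 1.0 and 120 replicates per scenario. The SDs and the pattern are assumptions. Absentees lost all treated-period values and kept all control-period values. The simulation standard error is about 0.03.

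| Absence mechanism | Nominal attendance | Full data | Mixed model, all available data | Completers only |
|---|---|---|---|---|
| Absentees gain nothing | 81% | −0.85 | −1.06 | −1.05 |
| Absentees gain nothing | 75% | −0.82 | −1.08 | −1.06 |
| Depends on observed baseline pain | 81% | −1.11 | −1.09 | −1.10 |
| Depends on observed baseline pain | 75% | −1.03 | −1.06 | −1.06 |

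When absence depends on observed baseline pain, the three analyses agree within simulation error. When absence goes with lack of benefit, the mixed model gives essentially the completers' answer.

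**Step 4: which outcomes are exposed.** The questionnaires supply pain intensity, work ability, self-efficacy, fear-avoidance, acceptance, depressive symptoms and sleep, which makes seven. Sickness-absence days and health care contacts come from the register and do not depend on attendance.

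**Step 5: Aft12m.** Section 2.5 puts completion in the meeting, while Section 2.7 has the form sent by mail. No arithmetic is needed to see that the mode is not fixed.

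**The case against.** The strongest objection is that the article says where the forms are normally filled in, and nowhere says that an absentee gets none. The trial already mails questionnaires, and chasing a missed visit is a detail that a condensed article may leave to the full protocol. This stands in part: that no route exists is an inference from silence. But the article does assign a mode to each form and names mail where it means mail. For Aft and Aft6m the mode it names, more than once, is the meeting.

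A reader might go further and infer the following, which the article does not support:

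- **That the analysis becomes a completers' analysis.** The mixed model keeps absentees' earlier values and is valid if absence depends only on observed data. Nor is the selection on completing treatment. Someone who skipped earlier sessions but came to the sixth is included, and someone who missed only the sixth is not.
- **That values are missing only in the treated state.** Bef1 for A, B and C and Bef2 for D, E and F are handed in at a first meeting, so someone who never attends could lack those too.
- **That filling in forms at the session adds a courtesy bias.** The article does not say who sees or collects the forms, and the researchers do not treat participants (Section 2.4). Unblinded self-report is inherent in a waiting-list trial of group therapy.
- **That the effect will be inflated by a quarter to a third.** That is the case in which absentees gain nothing at all.

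On Aft12m, mailing the form and then collecting it at the meeting would be one way to read the two sections together, but neither section says so.

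**Conclusion.** The point holds as a conditional risk confined to the seven questionnaire outcomes. As written, their post-intervention values depend on being present at two treatment meetings, and the plan's own participation figure makes absence likely enough to matter. The distortion is about nil if absence depends only on observed data, 10% to 14% if absentees get half the gain, and 23% to 33% if they get none.

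These sizes assume that the 75% to 81% carries over to presence at the meeting, and that absentees are not otherwise followed up. The 1.071 points is the design's minimum detectable difference and not an expected result. The disagreement over Aft12m is genuine and needs no assumption, but it concerns one time point in half the groups.

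**What to change.** In Section 2.5:

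- Keep in-meeting completion of Aft and Aft6m for attenders. Moving their forms home is not needed to solve the missing-data problem and might lower their return rate.
- In the same week, send the form to every allocated participant who missed that meeting or has stopped attending, with direct postal return that does not depend on any meeting, and one reminder.
- Give the same postal return to those who miss the first meeting, for Bef1 in A, B and C and for Bef2 in D, E and F.
- Analyse all 60 by allocated start.
- Reconcile Sections 2.5 and 2.7 so that Aft12m has one stated mode.

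The cost is postage and a reminder, with no change to the sample size, the intervention or the model. The drawback is that attenders and absentees will complete the forms in different settings.

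### Collecting the post-course and 6-month questionnaires at the sixth and seventh meetings ties seven of the nine outcomes to attendance and weakens the promised intention-to-treat analysis

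*Protocol article*

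**What the plan says.** All places are in the protocol article.

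- **Post-course form (Aft).** For groups A–C, 2.5 Timetable says: "The After (Aft) questionnaire is filled out during the sixth meeting". For groups D–F it says: "The Aft questionnaire is completed at the end of the sixth meeting". Table 1 (printed within 2.3) lists "Filling out the follow-up inquiry" as an activity of the sixth meeting.
- **6-month form (Aft6m).** 2.5 says: "Aft6m is filled out at the 6-month meeting". 2.7 Data collection repeats that this is the seventh meeting.
- **Forms by mail.** 2.5 says: "DEF groups are on the waiting list and get their Bef1 questionnaire by mail", to be returned in a week. Bef2 for D–F is also mailed, but is handed in at their first meeting. Bef1 for A–C is given out at the interview and handed in at their first meeting. For the 12-month form the two sections differ: 2.5 puts it in the meeting, 2.7 sends it by mail.
- **Expected participation.** 2.3 Randomization reports completion of 81% (CBT groups) and 75% (control groups) from a cited meta-analysis and adopts that range: "Consistently, we estimate those, who will take part in our study as ranging from 75% to 81" per cent. It declines to enlarge the sample for dropout.
- **Analysis.** 2.11 says: "Intention-to-treat analyses are conducted, and time-effect and intra-cluster correlation coefficients reported". The model is a linear mixed model for repeated measures.
- **Register outcomes.** Sickness-absence days and health-care contacts come from the occupational health records (2.7, 2.8), whatever the attendance.

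**The concern.** Presence at the sixth and seventh meetings is decided after randomisation and may depend on how the participant is doing. Someone who has stopped coming, or is absent that evening, has no stated way to return the form. Section 2.1 itself links missed meetings with lost follow-up when it justifies excluding severe disease.

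The clearest case is the nearest concurrent randomised contrast. The Aft form of A–C comes from people still present at the last session. It is set against the Bef1 form of D–F, mailed to everyone on the waiting list while A–C are in the course. If people whose pain has not improved are likelier to be absent, that contrast favours the course. Later data cannot repair it, because D–F have had the course by the time A–C reach six months. An analysis plan cannot recover forms that were never requested.

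**Working it through.** **1. Which outcomes are exposed.** Section 2.8 lists nine. Seven are from questionnaires: pain intensity, work ability, self-efficacy, fear-avoidance, acceptance, depressive symptoms and sleep. Two are from the register. So 9 − 2 = 7 depend on the meeting forms.

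**2. How many people.** Reading the adopted 75–81% as presence when the form is filled in (an assumption, because 2.3 gives no attendance figure for either meeting):

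- All groups: 60 × 0.19 = 11.4 and 60 × 0.25 = 15, so about 11–15 people without the form.
- Groups A–C: 30 × 0.19 = 5.7 and 30 × 0.25 = 7.5, so about 6–8 people.

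**3. Target effect.** Section 2.2 uses a 15% difference on a mean of 7.14: 0.15 × 7.14 = 1.071 points. The point does not rest on the sample size of 60.

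**4. Attenders' effect against the all-randomised effect.** With attendance share c, attenders' gain 1.071 and non-attenders' gain g, the all-randomised effect is c × 1.071 + (1 − c) × g. The values of g are assumptions.

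| g | c = 0.81 | c = 0.75 | Attenders' figure too high by |
|---|---|---|---|
| 0 | 0.868 | 0.803 | 23% to 33% |
| 0.5 | 0.963 | 0.928 | 11% to 15% |
| 1.071 | 1.071 | 1.071 | 0% |

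**5. Bias when the course has no effect.** The document gives no SD, correlation or absence mechanism. Assumed: pain SD 2; correlation 0.5 between any two measurements; and log-odds of absence rising by 0.5 or 1.0 per SD of current pain (odds ratio 1.6 or 2.7). I simulated 2 million people per side and regressed current pain on side and earlier pain among those with a form. All values are in points, in favour of the course.

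- One earlier measure, full return on the control side: 0.14 and 0.25 at 19% missing; 0.18 and 0.33 at 25% missing.
- Two earlier measures (Table 2 also records pain at screening), full return on the control side: 0.12–0.29.
- Control side losing half as many by the same mechanism, with one or two earlier measures: about 0.06–0.16.
- Equal loss on both sides, or absence unrelated to outcome: about nil.

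The non-zero results run from 0.06 to 0.33 points. Against the target, 0.06/1.071 = 6% and 0.33/1.071 = 31%.

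**The case against.** A reader might infer three stronger things, and the document supports none of them.

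- **That absentees are never asked.** The article states where the forms are filled in. It does not say that absentees go uncontacted, and a full protocol could add a route. This stands as a caution. Even so, the article fixes a place for each form, repeats it, and names mail where mail is meant, so following the text as written ties the forms to attendance.
- **That only the treated side loses data.** Bef1 for A–C and Bef2 for D–F are also handed in at a meeting, so only the D–F Bef1 form is free of any meeting. Mailed forms have non-responders too. Loss on the control side shrinks the bias, and equal loss by the same mechanism removes it. The pre-course forms do differ in one respect: their loss cannot depend on response to the course.
- **That the analysis becomes attenders-only.** The mixed model keeps the earlier records of people who later miss a meeting, and is valid if those records predict the absence. It fails only for absence driven by current pain or lack of benefit beyond what earlier answers predict.

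The rate is also uncertain. The 75% is the control-arm completion rate of the cited meta-analysis, and completing therapy is not the same as being present at the sixth meeting, or at one six months later. The upper figures above lean on that 75%.

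**Conclusion.** The point holds in a limited form. Collection as written makes the seven questionnaire outcomes, at the two main post-course times, depend on attendance after randomisation. This weakens the intention-to-treat analysis promised in 2.11, most clearly for Aft in A–C against the mailed Bef1 in D–F. The two register outcomes are safe.

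The document does not determine the size. Under the assumptions in steps 4 and 5, the null bias is about 0.06–0.33 points in favour of the course, and nil if absence is unrelated to outcome. The overstatement of a true 1.071-point effect runs from 0% to 23–33%; the top of that range needs non-attenders to gain nothing. None of these figures is a prediction for this trial. Because the loss cannot be undone once the meetings have passed and the remedy is small, this is a cheap improvement worth making.

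**What to change.** In 2.5 and 2.7, state that Aft and Aft6m are sought from every randomised participant whatever their attendance. Mail the same form within one week to anyone absent from the sixth or seventh meeting, including those who have stopped the course, with one reminder and a fixed return window. Tell participants at consent that stopping the meetings does not end the questionnaires. Include all returned forms in the intention-to-treat model, and report form return separately from attendance. Reconcile the 12-month form's route between 2.5 and 2.7 in the same edit.

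The cost is a few sentences of protocol and consent wording, plus postage and a reminder for perhaps 11–15 people at each of the two times, by a route the trial already uses. The small downside is that these forms arrive some days after the meeting.
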